**Methods**

After muscle biopsy the tissue will immediately be snap frozen in liquid nitrogen and stored at -70°C until analysis.

**Enzymehistochemistry and Immunohistochemistry**

Frozen sections of vastus lateralis muscle will be studied by standard histological procedures. Immunohistochemistry for endothelial and myogenic markers will be performed as previously reported (Ruger et al. 2004) with minor modifications. Acetone fixed sections will be blocked with avidin/biotin blocking reagent (Vector Laboratories, Burlingame, CA) and incubated overnight at 4°C with a rabbit anti-von Willebrand factor (vWF, 5.7 µg/ml, Dako), mouse anti-CD31 (4.5 µg/ml, Dako), mouse anti-CD34(0.5 µg/ml, Beckman Coulter, Immunotech, Marseille, France), mouse anti-CD133 (5 µg/ml, R&D Systems, Minneapolis, MN, detecting AC133-1 and AC133-2), and mouse anti-Pax7 (7.1 µg/ml, R&D Systems) diluted in Tris buffered saline (TBS)/1% bovine serum albumin (BSA). The reactivity of the primary unlabelled antibodies will be revealed using biotinylated goat F(ab’)2 anti-mouse IgG+IgM (H+L) (4.2 µg/ml, Jackson ImmunoResearch, West Grove, PA) or biotinylated donkey anti-rabbit IgG (H+L) (1.2 µg/ml, Jackson ImmunoResearch) diluted in 500 µg/ml normal human Ig (Biotest, Dreieich, Germany) followed by streptavidin-horseradish peroxidase (HRP) complex (20 µg/ml, Sigma, St. Louis, MO). For the detection of CD133 a supersensitive streptavidin-HRP conjugate (Biocare medical, Walnut Creek, CA) will be used. To visualize antibody staining the sections will be exposed to 3-amino-9-ethyl-carbazole (AEC, Sigma), and subsequently counterstained with Mayer’s hemalaun.

**Confokal Laser Scanning Microscopy**

4 µm thick frozen sections will be acetone fixed, blocked with avidin/biotin blocking reagent and 12.5% donkey serum, incubated overnight at 4°C with mouse anti-Pax7 or rabbit anti-vWF diluted in TBS/1% BSA, and subsequently incubated with 500 µg/ml normal human Ig and Alexa Fluor (AF) 555 donkey anti-mouse IgG (H+L) (for mouse anti-Pax7, all secondary AF antibodies 4 µg/ml, Invitrogen Life Technologies) or AF 555 donkey anti-rabbit IgG (H+L) (for rabbit anti-vWF). After blocking with 20% mouse serum (for anti-Pax7), tissue samples will then be incubated with fluorescein isothiocyanate (FITC)-conjugated anti-CD34 (2.5 µg/ml, Becton Dickinson PharMingen, San José, CA) diluted in TBS/1% BSA/5% mouse serum overnight at 4°C. An incubation with polyclonal goat anti-CD133 (2 µg/ml, Santa Cruz Biotechnology) overnight will be followed by a step using secondary antibody AF 647 donkey anti-goat IgG (H+L) (4 µg/ml, Invitrogen) which finishes the staining procedure. Stained samples will be covered with 4’, 6-diamidino-2-phenylindole (DAPI), diluted 1:4 with Vectashield mounting medium (Vector Laboratories). Sections will be analyzed with a confocal laser-scanning microscope (Zeiss LSM 510, Oberkochen, Germany) with a multiphoton laser (argon laser: 488 nm for FITC (green); Helium Neon (HeNe) 1: 543 nm for AF 555 (red); HeNe 2: 633 nm for AF 647 (blue)) and a 63 ´ Zeiss Plan-Apochromat differential interference contrast oil immersion objective with numerical aperture 1.40 using multitracking scan (Ruger et al. 2004).

**Morphometric analysis**

To quantify CD34+ and CD133+ progenitor cells, Pax7+ satellite cells, and CD31+ and von Willebrand factor+ mature endothelial cells 16 representative areas per section within the endomysium will be selected. Numbers of cells will be counted with a 40x objective using an ocular morphometric grid covering a total area of 1 mm2 (Wanschitz et al. 2003).

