Maintenance of adult skeletal muscle and regeneration upon damage is largely dependent on satellite cells, a population of tissue-resident committed myogenic progenitors, located in anatomical cell niches beneath the basal lamina of mature myofibers (Mauro 1961) (Schultz and McCormick 1994). After increased work-load or in response to muscle injury, satellite cells enter a well-defined sequence of activation, proliferation, myogenic differentiation and fusion events to repair or replace damaged muscle fibers (Buckingham et al. 2003). The entry of quiescent satellite cells into the myogenic differentiation program is critically regulated by the paired box transcription factors Pax3/Pax7 (Seale et al. 2000) (Relaix et al. 2005) (Zammit et al. 2006) and myogenic regulatory factors including Myf5, MyoD, myogenin and MRF4 (Tajbakhsh and Buckingham 2000) (Kassar-Duchossoy et al. 2004). Additionally sufficient vascularisation is crucial for the integrity and function of skeletal muscle. Increasing evidence by experimental studies suggests recruitment of bone-marrow derived circulating myogenic and endothelial progenitor cells which colonize skeletal muscle via the peripheral blood and contribute to postnatal myo-vasculogenesis. A subpopulation of primitive hematopoietic progenitor cells (HPCs), defined by the surface molecules CD34 and CD133 (Asahara et al. 1997) (Yin et al. 1997) (Gehling et al. 2000), has been found in adults with high potential to differentiate along myo-endothelial lineages *in vitro* (Pesce et al. 2003) (Torrente et al. 2004) and to contribute to regenerating muscle fibers (Jankowski et al. 2002) (Torrente et al. 2004) and neovascularization *in vivo* (Kawamoto et al. 2006). EPO is a potent stimulus for endothelial progenitor cell mobilization (Heeschen et al. 2003) and exhibits high angiogenic potential (Jaquet et al. 2002) (Urao et al. 2006), thus EPO might improve the regenerative capacity and function of skeletal muscle.

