**Studies of CD34+ and CD133+ hematopoietic progenitor cells in human skeletal muscle**

**Evidence for *in vivo* endothelial and myogenic differentiation of CD34+ and CD133+ hematopoietic progenitor cells in human skeletal muscle**

Using immunohistochemistry and reverse transcriptase-polymerase chain reaction (RT-PCR) we detected mononuclear cells expressing the early hematopoietic progenitor cell (HPC) markers CD34 and CD133 in human skeletal muscle of patients with inflammatory myopathies and normal controls without myopathy, who had a muscle biopsy for the exclusion of malignant hyperthermia. In the context of inflammation numbers of CD34+ and CD133+ mononuclear cells were significantly increased within the endomysial connective tissue contrasting with low numbers of these cells in controls without myopathy, suggesting that along with the infiltrating myelomonocytic cell population hematopoietic progenitor cells are mobilized from the bone marrow into the circulation and recruited to injured muscle to augment repair mechanisms following inflammatory damage. Several CD34+ interstitial cells co-expressed von Willebrand Factor at confocal laser scanning microscopy indicating in-situ maturation of CD34+ HPCs to the endothelial lineage. Occasionally, we observed mononuclear cells co-expressing CD133, CD34and Pax7, a marker of early myogenic differentiation, indicating myogenic commitment of some HPCs.

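### The Pax7+ count is not specific to satellite cells as the protocol itself defines them, so some progenitor recruitment could be reported as a satellite-cell rise

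*Protocol*

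**What the plan says.** The Morphometric analysis section lists its targets together: "To quantify CD34+ and CD133+ progenitor cells, Pax7+ satellite cells, and CD31+ and von Willebrand factor+ mature endothelial cells". It gives all of them one sampling frame, "16 representative areas per section within the endomysium will be selected", and one counting method: "Numbers of cells will be counted with a 40x objective using an ocular morphometric grid covering a total area of 1 mm2".

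Four other parts of the protocol bear on this rule.

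- **Skeletal muscle in FRDA** defines satellite cells by position, "located in anatomical cell niches beneath the basal lamina of mature myofibers", and ties Pax7 to them: "The entry of quiescent satellite cells into the myogenic differentiation program is critically regulated by the paired box transcription factors Pax3/Pax7".
- **Studies of CD34+ and CD133+ hematopoietic progenitor cells in human skeletal muscle** reports a second kind of Pax7+ cell: "Occasionally, we observed mononuclear cells co-expressing CD133, CD34and Pax7, a marker of early myogenic differentiation, indicating myogenic commitment of some HPCs".
- **The aims of the proposed study are**, aim 3, lists progenitor numbers and satellite cells as separate tissue outcomes.
- **The two staining sections** use antibodies to von Willebrand factor, CD31, CD34, CD133 and Pax7 for immunohistochemistry, and a Pax7, CD34 and CD133 combination with a nuclear stain for confocal microscopy. Neither names a basal-lamina marker.

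**The concern.** The background section identifies a satellite cell by where it lies, but the counting section identifies it by one marker. By the investigators' own preliminary observation, that marker is not exclusive to resident satellite cells. A cell positive for all three markers could therefore be counted as CD34+, as CD133+ and as a satellite cell.

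The error would run in the direction of the hypothesis. The protocol proposes that EPO mobilizes progenitors that settle in muscle. If some of them express Pax7, their arrival raises the satellite-cell figure even when the resident population has not changed. Two outcomes that aim 3 lists separately would then move together for a reason that lies in the counting rule. In an uncontrolled pilot of 5-7 patients, nothing else in the design would show that this had happened.

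The sampling frame adds an ambiguity. Endomysium can mean the connective tissue between fibres, which would leave out the sublaminal position, or the region of the section where fields are placed. Two readers could apply different rules to the baseline and week-8 sections.

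**Working it through.** The protocol gives no figure for this point, so there is none to reproduce. The check compares the protocol's statements and adds two short calculations.

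**1. Definition against counting rule**

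| Question | Protocol's answer | Where |
| --- | --- | --- |
| Where are satellite cells? | Under the basal lamina | Skeletal muscle in FRDA |
| How are they identified in the count? | Pax7+ | Morphometric analysis |
| Is a position required? | Not stated | Morphometric analysis |
| Can other cells be Pax7+? | Yes, occasionally, together with CD34 and CD133 | Preliminary studies |
| Are these excluded from the count or reported apart? | Not stated | Morphometric analysis |
| Is there a stain that shows co-expression? | Yes, confocal Pax7/CD34/CD133 | Confocal section |
| Is that stain tied to the count? | No: the count uses a 40x objective with an ocular grid, the confocal work a 63x objective | Both sections |
| Is there a stain that shows the basal lamina? | None named | Both staining sections |

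**2. Does the sampling frame exclude the fibre border?**

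Inputs from the protocol: 16 areas and a total of 1 mm². If 1 mm² is the sum over the areas, each is 1/16 = 0.0625 mm². A square field then has a side of √0.0625 = 0.25 mm, or 250 µm. The fibre diameter is not given; assume 40-80 µm. One side then spans 250/80 ≈ 3 to 250/40 ≈ 6 fibres. A field of that size contains fibre borders. If 1 mm² applies to each area, the field is larger still. The frame therefore need not exclude sublaminal cells, but the text does not say that they are to be counted.

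**3. How large could the contamination be?**

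All densities here are assumptions; the protocol gives none. Take 10 sublaminal Pax7+ cells per mm², unchanged by treatment, and *i* interstitial Pax7+ cells per mm² that triple. The pooled count goes from 10 + *i* to 10 + 3*i*, so

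relative rise = 2*i* / (10 + *i*).

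| *i* per 10 sublaminal | Calculation | Apparent rise |
| --- | --- | --- |
| 0.1 | 0.2/10.1 | 2% |
| 0.3 | 0.6/10.3 | 6% |
| 1 | 2/11 | 18% |
| 3 | 6/13 | 46% |

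The true satellite-cell change is 0% in every row. The first two rows fit better with cells seen only occasionally. At *i* = 1 to 3, interstitial cells would be 1/11 = 9% to 3/13 = 23% of all Pax7+ cells, which is hard to square with that word.

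**The case against.** A reader might infer that the count does not measure satellite cells at all: the niche is left out, only recruited cells remain, and a tripling of those would show as a 200% rise, (3*i* − *i*)/*i*. The protocol does not support this. It links Pax7 to satellite cells itself, and fields of about 250 µm among the fibres would plausibly take in fibre borders.

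A reader might also infer that the protocol demonstrates blood-derived Pax7+ cells in this disease. It does not. The triple-positive cells came from work on inflammatory myopathies and on controls without myopathy, not from FRDA muscle. The account that "hematopoietic progenitor cells are mobilized from the bone marrow into the circulation and recruited to injured muscle" is offered there as a suggestion. Nor does that section say where the triple-positive cells lie, so calling them interstitial is an assumption.

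It can further be said that the planned confocal staining detects exactly this phenotype. That is correct, and the co-expression problem can be solved with reagents already chosen. What remains is that the counting section does not use that staining. The single-chromogen immunohistochemistry, which appears to be the source of the counts, describes no co-labelling.

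Finally, satellite cells are one of several exploratory tissue measures in a small pilot, and the counting method cites a publication not available here that may contain more detail. Both points limit the weight of the concern. Neither tells a reader of this protocol which Pax7+ cells count as satellite cells.

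**Conclusion.** The concern holds in a limited form. The Pax7+ count is not specific to satellite cells as the protocol defines them: it has no positional criterion, its region can be read in two ways, and Pax7+ cells that also carry CD34 or CD133 are not separated. Some progenitor recruitment under rhuEPO could therefore be reported as a rise in satellite cells.

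The size is unknown and probably small. The 2-6% range assumes 0.1-0.3 interstitial cells per 10 sublaminal ones, a tripling of the interstitial cells, and pooling of both kinds. The 18-46% range needs ten times that density, for which the document offers no basis. This is an inexpensive gain in the specificity of one exploratory outcome; it does not invalidate the outcome.

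**What to change.** In the Morphometric analysis section:

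1. State that Pax7+ cells are counted over whole grid fields, including fibre borders, and say whether 1 mm² is the total over the 16 areas.
2. Use the Pax7/CD34/CD133 confocal staining already planned to report two numbers: Pax7+ cells positive for CD34 or CD133, and Pax7+ cells negative for both.
3. Preferably, add a basal-lamina counterstain (laminin) to the existing Pax7 sections, and report sublaminal and interstitial Pax7+ nuclei separately.
4. Apply the same rule to the baseline and week-8 sections.

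The report should add that position does not prove origin. The background section itself allows that circulating progenitors contribute to regenerating fibres, so a sublaminal nucleus is not necessarily resident, and steps 2 and 3 complement each other.

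The cost is a few sentences, some extra reading time and at most one additional stain, on tissue that is already being collected.

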**Study Design**

This is a single centre, non randomized pilot study.

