**Patients and Investigations**

Seven adult subjects with definite FRDA will be enroled in this study. Skeletal muscle will be obtained by an open biopsy from at baseline (untreated) and after 2 months of rhuEPO treatment after written informed consent.

Treatment encompasses rhuEPO 3.000 IU (~100 IU/kg KG) three times weekly subcutaneously for 8 weeks.

Specimen from the quadriceps muscle and MR spectroscopy from the contralateral side will be obtained pre- and post rhuEPO treatment.

Frataxin-levels will be assessed in lymphocytes and muscle specimen at baseline and study end-point. Furthermore, FACS analysis of circulating CD34+ and CD133+ cells in peripheral blood will be perfomed bi-weekly. The numbers of CD34+ and CD133+ cells and capillary density per mm2 will be quantified in skeletal muscle at baseline and after 8 weeks EPO treatment.

Biochemically, complex I, II, and III of the respiratory chain in the quadriceps muscle will be evaluated pre-and post treatment.

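### Fields for the muscle histology counts are left to judgement, and no masked reading is provided for, although an uncontrolled before/after contrast is all that supports these parts of aim 3

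*Protocol*

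**What the plan says.** Under Morphometric analysis the protocol lists the targets of the count, "To quantify CD34+ and CD133+ progenitor cells, Pax7+ satellite cells, and CD31+ and von Willebrand factor+ mature endothelial cells", and then states that "16 representative areas per section within the endomysium will be selected". Counting is done "using an ocular morphometric grid covering a total area of 1 mm2", and an earlier publication is cited. The section does not say who selects the areas, by what rule, or whether that person knows if the slide is from before or after treatment. No other section mentions coding or masked reading of slides.

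The comparison that these counts feed is set out under Patients and Investigations. Muscle is taken "at baseline (untreated) and after 2 months of rhuEPO treatment", and "cells and capillary density per mm2 will be quantified in skeletal muscle at baseline and after 8 weeks EPO treatment". Study Design reads "This is a single centre, non randomized pilot study". One regimen is described for all patients and no control group is mentioned. The number of patients is 5-7 under Number of patients and seven under Patients and Investigations. Under Methods, tissue is snap frozen and "stored at -70°C until analysis".

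Aim 3 asks for the effect of treatment on frataxin expression, progenitor cells, satellite cells, capillary density and respiratory chain activity in muscle.

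**The concern.** Selecting areas because they look representative is a judgement, and cell counts depend on it. Sixteen areas totalling 1 mm2 are 0.0625 mm2 each, so for a sparse cell type a few fields can decide the result. The protocol's summary of the investigators' own earlier work reports low numbers of CD34+ and CD133+ cells in muscle without myopathy. If muscle in FRDA is similar, those two counts are the most exposed.

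In a randomised, masked comparison, loose field selection would mostly add noise. Here each patient contributes one untreated and one treated biopsy and there is no parallel group. Any systematic difference between the two time points in how fields are chosen, or in staining or reading, therefore falls on the treatment contrast, and no later analysis can remove it. It may run either way, creating an apparent rise or concealing a real one.

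This is a matter of laboratory method and study conduct, which a statistical analysis plan would not normally supply.

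**Working it through.** The protocol states no SD, expected count, effect size or significance level for these endpoints, so it has no figure to reproduce. The check asks how far a modest selection shift could move the result.

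**From the protocol:** 16 areas, 1 mm2 in total, 5-7 patients, two biopsies per patient.

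**Assumed:**
- there is no true change;
- fields on treated slides are richer in cells by a fraction b = 20% or 30%;
- the within-patient SD of the log after/before ratio is s = 0.3, 0.5 or 0.7;
- the test is a two-sided 5% paired t-test on log ratios. Statistical analysis does not name this test.

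**Area per field:** 1 mm2 / 16 = 0.0625 mm2, a square of 250 µm side. The section is consistent with itself.

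**False-positive rate:** the test statistic follows a non-central t with n − 1 degrees of freedom and non-centrality ln(1 + b) / (s/√n). Here ln 1.2 = 0.182 and ln 1.3 = 0.262. The two-sided critical values are 2.776 (n=5, 4 df) and 2.447 (n=7, 6 df).

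Example: for n=7, s=0.3 and b=20%, the non-centrality is 0.182 / (0.3/√7) = 1.61, and the probability of exceeding ±2.447 is 27%.

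| SD of log ratio | n=5, b=20% | n=5, b=30% | n=7, b=20% | n=7, b=30% |
|---|---|---|---|---|
| 0.3 | 18% | 32% | 27% | 49% |
| 0.5 | 10% | 15% | 13% | 22% |
| 0.7 | 7% | 10% | 9% | 13% |

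All entries exceed 5%, some only slightly.

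**Which SD is plausible:** with an assumed 5 cells per mm2 at each time point, Poisson variation alone gives a log-ratio SD of about √(1/5 + 1/5) = 0.63. The lower rows therefore suit rare progenitor cells better. SD 0.3 is more plausible for abundant structures such as capillaries.

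**Second route:** a simulation of 2,000 trials per setting assumed no true change, 48 available fields per section, on average 1 or 3 cells per field, and the same paired t-test on log ratios.
- With 16 fields taken at random at both time points, the mean ratio was 0.99-1.01 and the false-positive rate 4.5-6.0%.
- With a weak preference for cell-rich fields on treated slides only (log-weight 0.25 per SD of field count), the apparent rise was 20-27% and the false-positive rate 12-18% over n=5 and n=7.

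So a 20% shift does not need gross selection, and random field choice brings the rate back to about nominal.

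**The case against.** **The text does not say that anything is done badly.** A reader might infer that fields are hand-picked by someone who knows the time point. The documents do not support that: they do not say who selects, with what knowledge or in what order, and the cited counting method might contain a sampling rule. This objection stands. What remains is that this protocol fixes a discretionary rule and offers no protection around it.

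**The larger percentages depend on favourable choices.** This also stands. The 20-30% shifts are assumed, n=7 is the upper end of the range, and the argument from sparse cells implies a larger SD and so a smaller inflation. Statistical analysis names ANOVA, Kruskal-Wallis and Mann-Whitney tests, not a paired test, so none of the figures is the error rate of the analysis as written.

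**The evidence on sparse cells is indirect.** The low counts come from controls without myopathy. No figure is given for FRDA muscle, for Pax7+ cells or for capillaries.

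**Little depends on it in a pilot.** In part. No success rule is stated, and frataxin, enzyme activities, FACS and spectroscopy do not depend on field choice. The CD34+, CD133+, satellite-cell and capillary results in muscle do.

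**Density per mm2.** A reader might also infer that counting per mm2 is itself an error, because density changes with fibre size: fibres 10% wider or narrower change it by 1/1.1² − 1 = −17% or 1/0.9² − 1 = +23%. That does not hold as a criticism. Differences in fibre size that vary in sign between patients add noise, not bias. Nothing in the protocol suggests a common shift over 8 weeks, and density per mm2 is a coherent scale that matches the stated aim.

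**Conclusion.** The point holds in a limited form. The protocol fixes a discretionary choice of fields and does not provide for masked reading, while an uncontrolled before/after comparison in 5-7 patients carries the histology part of aim 3. A selection shift linked to the time point would be inseparable from a treatment effect.

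How large that shift would be in this trial cannot be derived. On the stated assumptions the false-positive rate lies between 7% (n=5, SD 0.7, 20% shift) and 49% (n=7, SD 0.3, 30% shift), with the lower part of that range more apt for rare cells. These figures show what the plan leaves open, not that bias will occur. The change is worth making because it is cheap and because open biopsies in so few patients are hard to repeat.

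**What to change.** In Morphometric analysis, replace the selection of representative areas with 16 fields placed by systematic uniform random sampling within the section: a random start and a fixed step. The counted area stays at 1 mm2.

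Add that both biopsies of each patient are stained in the same run after the last re-biopsy, that slides are coded, and that one reader, unaware of time point, reads them in mixed order. Frozen storage already makes this possible.

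Cost: a coding list and a written sampling rule, with no additional biopsy, patient or reader. The downside is that histology results wait until the last re-biopsy.

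Optionally, count fibres in the same fields and show per-fibre values beside those per mm2. That is a sensitivity display, not the correction of an error.
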